### Blinding of the study

Only the researcher responsible for administering the treatments (who will open the randomization envelopes) will know which treatment is assigned to each side of the patient. Group identities will be revealed after the statistical analysis of the data to all those involved in the study. Therefore, the researcher responsible for data collection, patient, and statistician will be blinded to the treatments assigned to the groups.

Surgery will be performed conventionally, with the LED/laser turned off in the control group. However, the same points will be treated in the pre-operative (baseline) period as in the experimental group. To prevent the patient from identifying non-activation based on sound of the device, the sound will be recorded and played during the simulation. This blinding method ensures that the participants, data collectors, and statistician remain unaware of the treatment assignments throughout the study. The main investigator will obtain informed consent from potential trial participants. Procedures for collecting, sharing, and safeguarding personal information of potential and enrolled participants will be implemented to ensure confidentiality throughout the trial, both during and after its completion.

### Preoperative assessment

All participants who meet the eligibility criteria for the study and sign the statement of informed consent will undergo a preoperative assessment, which will involve the initial measurement (baseline, pre-surgery) of all study outcomes. These assessments will be conducted by a trained researcher for objective outcomes and a calibrated researcher for subjective outcomes. Surgery will proceed as usual, similar to conventional third molar surgery.

### Surgical procedures

One hour after photobiomodulation (t = 0), the participants will undergo the removal of the third molar by a surgeon following the standard technique at the Catholic University of Uruguay.

A local anesthetic will be administered to the inferior alveolar, lingual, and buccal nerves using two 1.8 ml carpules containing 2% mepivacaine with epinephrine 1:100,000 (MEPIADRE 100, DFL, Brazil). An intrasulcular incision will be made with a No. 15 scalpel blade (BIOSET, China) on the buccal side of the second lower molar, extending distally and laterally toward the anterior edge of the mandibular ascending ramus. A triangular periosteal mucosal flap will be dissected using a Molt No. 9 periosteal elevator (HU-FRIEDY, USA).

The buccal and distal bone will be removed using a No. 8 round tungsten carbide bur (STRAUSS AND CO., Israel) and low-speed surgical micromotor (BIOMET 3i, OSSEOCISION NE 111, Japan), with abundant irrigation using 0.95% saline solution. If necessary, coronal and/or interradicular tooth sectioning will be performed using a No. 703 tungsten carbide bur (STRAUSS AND CO., Israel) at low speed and with constant irrigation.

After extraction, thorough cleaning of the residual surgical cavity will be performed, followed by repositioning, and suturing the mucosal flap with 3–0 silk thread (BESTCARE, Portugal) mounted on a disposable circular-section needle (BESTCARE, Portugal).

### Medication protocols in the preoperative period

Control Group: Dexamethasone 8 mg, 1 tablet administered 1 hour before surgery.

Experimental Group: Photobiomodulation applied intraorally and extraorally 1 hour before surgery (detailed in the "Photobiomodulation method" section).

Medication protocols in the postoperative period (both groups):

Amoxicillin 750 mg tablet, orally every 12 hours for 7 days.

Anti-inflammatory medication: Ketorolac 10 mg every 6 hours for 3 days.

Analgesic medication: Paracetamol 500 mg every 6 hours for 3 days to be taken in the occurrence of pain (number of tablets taken will be quantified as a secondary outcome).

### Experimental design

Prior to the surgical procedure, the researcher responsible for treatment will open an envelope (without altering the numerical sequence of the remaining envelopes) and perform the procedure indicated. The 30 individuals will be allocated to the experimental and control groups as follows (Fig 1):

**Fig 1 pone.0300136.g001:**
[figure not shown]
Flowchart of study. VAS—visual analog scale.

Control Group (n = 30 surgeries)—Individuals will receive conventional treatment with dexamethasone 8 mg orally 1 hour prior to surgery [13] + simulated photobiomodulation. The laser will be turned off and will be applied at the same points as in the experimental group in the immediate preoperative period (baseline).

Experimental Group (n = 30 surgeries)*—*Participants will receive photobiomodulation 1 hour prior to the surgical procedure + a placebo tablet of dexamethasone (Laboratory Matías Gonzalez, Montevideo).

Photobiomodulation method—All participants and researchers will wear individual protective glasses during the applications and simulations.

Intraoral photobiomodulation—In the photobiomodulation Group, intraoral irradiations will be performed with a low-intensity laser at a wavelength of 660nm (power of 0.1W, radiant exposure of 1061 J/cm^2^, and energy of 3 J per point, with a 30-second duration at each point, totaling 12J). The same four points will also be irradiated using a wavelength of 808nm (power of 0.1W, radiant exposure of 1061 J/cm^2^, and energy of 3 J per point, with a 30-second duration at each point, totaling 12J), adapted from Sierra et al., 2015 [24].

Photobiomodulation method

All participants and researchers will use protective eyewear during the applications and simulations.

Intraoral photobiomodulation—In the photobiomodulation group, intraoral irradiation (4 points) will be performed with a low-intensity laser at a wavelength of 660 nm (power of 0.1 W, radiant exposure of 1061 J/cm^2^, and energy of 3 J per point, with a 30-second duration at each point, totaling 12 J). The same four points will also be irradiated using a wavelength of 808 nm (power of 0.1W, radiant exposure of 1061 J/cm^2^, and energy of 3 J per point, with a 30-second duration at each point, totaling 12 J), adapted from Sierra et al. (2015) [24].

Intraoral irradiation (Table 1) will be performed by placing the laser head directly in contact with four points on the lingual mucosa in the surgical field (alveolus of the tooth to be extracted): At the site where the suture will be performed (middle of the bone socket), on the lingual surface (cervical third), on the lingual surface (middle third), and on the lingual surface (apical third).

**Table 1 pone.0300136.t001:** Parameters of intraoral photobiomodulation.

Parameters	Red Laser	Infrared Laser
Wavelength (nm)—Central wavelength	660	808
Operating Mode	Continuous	Continuous
Spectral Bandwidth (nm)	5	5
Average Radiant Power (W)	0,1	0,1
Polarization	Random	Random
Irradiance at the target per point (W/cm^2^)	35	35
Beam Area at the target (cm^2^)	0,002827	0,002827
Exposure Time per Point (s)	30	30
Radiant Exposure at the target tissue per point (J/cm^2^)	1061	1061
Radiant Energy per Point (J)	3	3
Total Radiant Energy (J)	12	12
Irradiated Points	4 points	4 points
Number of Sessions and Frequency	Single session	Single session
Application Technique	contact	contact

J-Joules, W-Watt

Simulated irradiation will be performed at the same points described earlier. This protocol will be applied one hour prior to surgery.

Extraoral photobiomodulation*—*The extraoral photobiomodulation will be applied using a cluster with a contact area of 20 cm^2^ over the insertion point of the masseter muscle.

Extraoral photobiomodulation*—*Extraoral photobiomodulation will be applied using a cluster with a contact area of 20 cm^2^ over the insertion point of the masseter muscle. The cluster will be of the brand Ibramed (Amparo, São Paulo, Brazil), model Antares (small cluster 2). Irradiation will be performed [21, 25] using the cluster of 5 LEDs with a wavelength of 630 nm (power of 0.25 W per LED, radiant exposure of 3 J/cm^2^, and energy of 12 J, with a total time of 48 seconds, totaling 60 J of energy). The same region will then be irradiated with the cluster of 4 LEDs with a wavelength of 850 nm (power of 0.3W per LED, radiant exposure of 2.4 J/cm^2^, and energy of 12 J per point, with a total time of 40 seconds, totaling 48 J of energy). This protocol will be applied one hour prior to surgery (Table 2).

**Table 2 pone.0300136.t002:** Parameters of extraoral photobiomodulation.

Parameter	Red LED Vermelho	Infrared LED
Central Wavelength (nm)	630	850
Operating Mode	Continuous	Continuous
Spectral Bandwidth	20nm	35nm
Average Radiant Power (W) per LED	0,25	0,3
Total Power (W)	1,25	1,20
Polarization	random	random
Irradiance at the Target Tissue (W/cm^2^)	0,06	0,06
Beam Area at the Target Tissue (cm^2^)	20	20
Exposure Time (s)	48	40
Radiant Exposure at the Target Tissue (J/cm^2^)	3	2,4
Radiant Energy (J)	12	12
Total Energy per Cluster	60	48
Number of Points Irradiated	5 points	4 points
Number of Sessions and Frequency	Single session	Single session
Application Technique	contact	contact

J-Joules, W-Watt

Individuals who experience any complications during the research period, such as allergic reactions to any of the materials used, an allergic reaction to Paracetamol®, or having taken any other drug not provided, those who, in any way, become unable to attend the appointments on the scheduled dates, relocate to a different city, or simply no longer wish to participate in the research will be excluded from the study but will not suffer any negative consequences in terms of treatment.

The data of all participants will be included in the statistical analysis, described, and discussed, along with any potential major and minor adverse effects.

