### Sample size calculation

The sample size was calculated to provide an 80% power (α = 0.05). The sample size will consist of 30 surgeries per group. Thirty patients with bilateral and symmetric lower third molars (right and left) will be selected. The procedure will then be performed randomly (split-mouth design), totaling 60 surgeries (30 surgeries in the control group and 30 surgeries in the experimental group). For the calculation, we used the 48-hour time point in the article by Aras and Güngörmüş (2010) [21]. The average edema measurement was 105 mm in the control group and 109 mm in the experimental group. The larger standard deviation between the two means ±5 mm was chosen for the sample size calculation.

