Exclusion of individuals—if they have local conditions that contraindicate surgical intervention or could complicate the post-operative period, such as acute pericoronitis in the previous 30 days or temporomandibular joint ankylosis. Smokers, individuals lacking both upper and lower central incisors, those with a history of photosensitivity, pregnant or lactating women, and individuals using anti-inflammatory drugs or analgesics and those with allergies to any drugs used in the study (e.g., paracetamol, 2% chlorhexidine, local anesthetics, sodium bisulfite) will also be excluded. Individuals experiencing surgical complications, such as bleeding or operative difficulties, will be ineligible for the study due to the potential impact on maintaining the expected surgical standards and the accuracy of the study outcomes. Participants undergoing surgical procedures lasting longer than 90 minutes will be excluded from the study. Surgeries lasting longer than 90 minutes could potentially impact the accuracy and reliability of the findings due to the likelihood of increased post-operative trauma, which may result in more significant edema and pain.

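### Exclusions triggered by events after allocation, one of them justified by expected edema and pain, conflict with the promise to analyse all participants and can bias the comparison

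*Protocol article*

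**What the plan says.** Protocol article, Participant characterization, in the paragraph on exclusions: "Participants undergoing surgical procedures lasting longer than 90 minutes will be excluded from the study", and "Individuals experiencing surgical complications, such as bleeding or operative difficulties, will be ineligible for the study". The reason given for the time limit is that longer operations mean more trauma and hence more edema and pain. The reason given for the complication rule is to protect surgical standards and the accuracy of the outcomes.

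Experimental design, first closing paragraph after Table 2: people with any complication during the research period are excluded from the study. So are those "having taken any other drug not provided, those who, in any way, become unable to attend the appointments on the scheduled dates", those who move to another city and those who no longer wish to take part.

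The next paragraph states: "The data of all participants will be included in the statistical analysis".

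Randomization places the opening of the envelope just before surgery. The medication and photobiomodulation sections place treatment one hour before surgery. The first operation is on the right side, and the left side later receives the opposite treatment.

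**The concern.** Operating time, bleeding, operative difficulty, complications, use of other drugs and missed visits cannot be known when the envelope is opened. Some are written as eligibility criteria, but they act as post-randomisation exclusions.

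Several are plausibly linked to what is being measured. The article itself links the 90-minute rule to edema (primary) and pain (secondary). A patient with more pain or swelling is more likely to take a drug that was not provided. Hematoma/ecchymosis is a secondary outcome, so excluding for bleeding can remove information on it.

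Two things are at stake. First, the comparison would be conditioned on events after treatment and would no longer be the randomised one. Second, the analyst could keep or drop a patient with high edema and cite the article either way. The split-mouth design adds to this: a patient excluded after the first operation may never contribute the second side, and the article does not say what becomes of the side already measured.

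**Working it through.** **1. Order of events.** The envelope is opened just before surgery (Randomization) and treatment is given one hour before surgery (medication section). Then comes the operation, where duration, bleeding and difficulty are first known. Follow-up to day 7 comes next, where complications, other drugs and missed visits are first known. Every trigger examined here follows allocation and treatment.

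**2. The sections side by side.** Participant characterization removes people so that long or difficult operations do not affect the findings, which only makes sense if their data leave the analysis. Experimental design then says that all participants' data are analysed. If both rules govern the analysis, a patient with a 100-minute operation is both out and in.

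**3. The plan's own figure.** Sample size calculation gives "The sample size was calculated to provide an 80% power (α = 0.05"), means of 105 and 109 mm (difference 4 mm), SD 5 mm and 30 surgeries per group. Taking a two-sided test (sidedness is not stated):

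n per group = 2 × (1.960 + 0.842)² × 5² / 4² = 2 × 7.85 × 25/16 = 24.5, so 25; the exact t-test gives 26.

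For a paired test, SD of the difference = 5 × √(2(1 − ρ)). With ρ = 0 this is 7.07 mm and 27 pairs are needed; with ρ = 0.5 it is 5.00 mm and 15 pairs. The figure of 30 is not reproduced, but it exceeds the need and does not bear on this point.

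**4. Possible size of the bias.** The article gives no exclusion rate, selection strength or within-patient correlation ρ, so these are assumptions. In a simulation of 400,000 split-mouth pairs (normal, SD 5 mm per side, true difference 4 mm), the same rule applied to both arms. The estimated difference in mm was:

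| Assumed exclusion rule | ρ | 5% dropped | 10% dropped | 20% dropped |
|---|---|---|---|---|
| Patients with the highest edema on either side, both sides dropped | 0 | 3.59 | 3.33 | 2.92 |
| Same | 0.5 | 3.79 | 3.64 | 3.39 |
| Only the sides with highest edema dropped | 0 | 3.34 | 2.95 | 2.41 |
| Weaker: log-odds of exclusion rise by 1 per SD of edema, whole patient dropped | 0 | 3.90 | 3.83 | 3.69 |
| Same, weaker | 0.5 | 3.96 | 3.93 | 3.86 |

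As a share of 4 mm, the first row loses (4 − 3.59)/4 = 10% to (4 − 2.92)/4 = 27%. The second loses 5% to 15%, and the weaker-selection rows 1% to 8%. With a true difference of 0, every rule gave a bias within 0.01 mm of zero.

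**5. Power.** With 30 pairs, paired power is 85% (ρ = 0) or 99% (ρ = 0.5). If 10%, 20% or 30% of patients are lost (27, 24 or 21 pairs), it is 81%, 76% or 69% at ρ = 0, and 98%, 96% or 94% at ρ = 0.5.

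**The case against.** The strongest reply is that the paragraph in Experimental design is about withdrawal. It lists relocation and loss of willingness beside the other triggers and reassures people about their care. The sentence on analysing everyone comes directly after it. On that reading, participation stops and the data already collected stay in. This is a fair reading of that section alone, and relocation need not be related to outcome. It does not rescue Participant characterization, whose stated reasons point to removing data.

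Blinding also helps. Apart from the researcher giving treatment, those involved are meant not to know the allocation, so calls on duration or difficulty should not favour an arm by intent. That limits deliberate imbalance, but not selection through the outcome itself, which shrinks a true difference even under a symmetric rule.

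A reader might infer more than the article supports:

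- *That one arm's mean is shifted by 0.54, 0.97 or 1.75 mm.* This is SD × φ(z)/(1 − f) for f = 5%, 10%, 20%: 0.109, 0.195 and 0.350 times 5 mm. It needs exclusion of exactly the worst sides in one arm only. No trigger is an edema threshold, and nothing says exclusions would be one-sided. If whole pairs are dropped and ρ = 0.5, the shift in the difference halves.
- *That the trial would fall below 80% power.* Independent 10% loss by side keeps 0.9² = 81% of pairs, about 24, against 27 needed at ρ = 0. But the rules exclude people rather than sides, and 24 pairs still give 89% power at ρ = 0.3.
- *That corticosteroid side effects make removal unequal.* The Introduction stresses prolonged use. The control treatment is a single preoperative tablet, so this is weak support.

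**Conclusion.** The point stands in this form: the article states post-allocation exclusions, ties at least one of them to the primary outcome, and contradicts them with a promise of full inclusion. This is wrong as written and must be reconciled; it is not a detail left to an analysis plan.

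The effect is that the exclusions can bias the comparison. That they will is not shown. Under the assumed patient-level selection, a true 4 mm difference falls to 3.6–2.9 mm (ρ = 0) or 3.8–3.4 mm (ρ = 0.5). It falls to 3.7–4.0 mm under weaker selection, and there is no bias with symmetric selection and no true difference. The rates, selection strength and ρ are all assumed.

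The direction under a symmetric rule matters here because the comparator is active. Shrinkage toward no difference could make photobiomodulation look closer to dexamethasone than it is, and the Discussion already presents it as an alternative. Power loss is a secondary matter and is material only if ρ is near zero.

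**What to change.** 1. Limit the eligibility criteria to facts known before the envelope is opened.
2. Separate stopping participation from leaving the analysis, and say so in both sections.
3. Define the primary analysis set as all randomised patients, with each side analysed under its randomised treatment. Use all data collected, including patients with only one side measured, whatever the length of surgery, complications or other drugs taken. Continue follow-up unless consent is withdrawn; it cannot be required of those who withdraw.
4. Keep the exclusions listed in Participant characterization and Experimental design only as a labelled sensitivity analysis, and report these events by arm.
5. Reword the two sections so that they agree with the sentence on analysing all participants.

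The cost is protocol wording, some further follow-up and one extra analysis. The downside is some added variance from long or complicated operations.

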### Study outcomes

The primary outcome of the study will be:

Edema—three measurements will be taken on the patient’s face with a previously sanitized flexible measuring tape: tragus-pogonion, tragus-labial commissure, and mandibular angle-outer orbital commissure [26]. Measurements will be taken immediately before surgery as well as two and seven days after surgery.

The secondary outcomes of the study will be:

Pain Sensitivity*—*The visual analog scale (VAS) is the most widely used instrument for measuring postoperative pain after oral surgeries with photobiomodulation in the postoperative period [24, 26]. In this study, the VAS will be used immediately after surgery as well as two and seven days after surgery [24, 26] using 10-cm line with "0" (no pain) at one end and "10" (unbearable pain) at the other. Instructions on marking will be provided to the patient by the same operator.

Quantity of pain tablets taken during the period*—*The number of analgesic tablets taken at two and seven days will be counted. All participants will take paracetamol and be instructed to take it every six hours only in the presence of pain [27]. At the beginning of the study, each participant will be provided a paracetamol tablet, which is a drug with purely analgesic effects [28]. At the end of the experiment, the quantity of tablets will be evaluated as a secondary outcome. Patient adherence will be monitored. For such, the patients will be asked to bring the medication blister pack to the appointment to check how it is being used.

Postoperative trismus assessment*—*Spasms in the masticatory muscles (trismus) can limit or even prevent mouth opening after the surgical removal of impacted third molars [21, 23, 29]. This outcome is typically evaluated by measuring the distance between the incisal edges of the upper and lower central incisors using calipers [27, 29]. In this study, previously calibrated evaluators will measure mouth opening in each patient before surgery as well as two and seven days after surgery.

Impact of the surgical procedure on quality of life*—*Two previously calibrated evaluators will ask patients to respond with "yes" or "no" to the following 10 questions two and seven days after surgery, as described by Sierra et al. (2013) [26] and Sierra et al. (2015) [24].

The 10 questions were:

Are you maintaining your social activities normally?

Are you working/studying normally?

Are you maintaining your regular diet?

Do you have difficulty swallowing due to the surgery?

Do you have difficulty tasting food?

Can you chew on the operated side?

Do you have difficulty sleeping due to the surgery?

Did you have difficulty speaking due to the surgery?

Has your appearance changed due to the surgery?

Do you experience nausea due to the surgery?

Dysphagia—The assessment of dysphagia will be conducted two and seven days after surgery through questions [27] and classification on a numerical scale: (0) total absence of dysphagia; (1) dysphagia for solid foods; (2) dysphagia for any liquid or solid food.

Assessment of the presence and intensity of hematoma/ecchymosis*—*The presence of hematoma/ecchymosis will be assessed by measuring the largest diameter of color changes on the skin of the cheek and submandibular region at two and seven days after surgery. The measurement will be performed by a previously calibrated evaluator, who will classify the occurrence of this event in four categories: (1) non-existent; (2) largest diameter less than 4 cm; (3) largest diameter between 4 and 10 cm; and (4) largest diameter greater than 10 cm, as described by Bjornsson et al. (2003) [30].

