## Abstract

Photobiomodulation is a safe option for controlling pain, edema, and trismus when applied postoperatively in third molar surgery. However, administration prior to surgery has been under-explored. This study aims to explore the effectiveness of pre-emptive photobiomodulation in reducing postoperative edema in impacted lower third molar extractions. Two groups of healthy individuals undergoing tooth extraction will be randomly assigned: Control group receiving pre-emptive corticosteroid and simulated photobiomodulation, and Photobiomodulation Group receiving intraoral low-intensity laser and extraoral LED cluster application. The primary outcome will be postoperative edema after 48 h. The secondary outcomes will be pain, trismus dysphagia, and analgesic intake (paracetamol). These outcomes will be assessed at baseline as well as two and seven days after surgery. Adverse effects will be recorded. Data will be presented as means ± SD and a p-value < 0.05 will be indicative of statistical significance.

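### Each facial distance in the primary edema outcome is read once per visit; averaging two readings would be a cheap, optional gain in precision, small to moderate in size

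*Protocol article*

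**What the plan says.** The Abstract sets the primary time point: "The primary outcome will be postoperative edema after 48 h". Under Study outcomes, edema is assessed by a fixed number of readings, "three measurements will be taken on the patient’s face", and the three are then named as separate distances, taken "with a previously sanitized flexible measuring tape: tragus-pogonion, tragus-labial commissure, and mandibular angle-outer orbital commissure [26". The schedule is baseline and two later visits: "Measurements will be taken immediately before surgery as well as two and seven days after surgery". No repeat reading or averaging of repeats is mentioned.

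For trismus the same section says that "previously calibrated evaluators will measure mouth opening in each patient before surgery as well as two and seven days after surgery". It gives no number of readings.

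Sample size calculation plans a split-mouth trial of 30 patients from 48 h values: "The average edema measurement was 105 mm in the control group and 109 mm in the experimental group", with "The larger standard deviation between the two means ±5 mm was chosen for the sample size calculation". Calibration and examiner training provides joint training and an intraclass correlation check on 10 volunteers outside the sample, without a figure for reading error. It also gives the pre-operative and post-operative measurements to different examiners. Statistical analyses does not say whether edema is analysed as a change or as a 48 h value, and the article does not say how the three distances are combined.

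**The concern.** A tape laid over soft tissue between landmarks gives a reading with some random error, and swelling can make the landmarks harder to find. The count of three is used up by three different distances, so nothing in the stated method dilutes that error within a distance. The split-mouth design removes stable differences between patients, so reading error forms a larger share of the remaining variance than it would in a parallel-group trial. How large that share is cannot be told from the article.

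What is at stake is the width of the confidence interval for the primary comparison. The number of pairs is fixed at 30, and the examiner is already with the patient at each visit. A second reading is one of the few ways to narrow the interval without enrolling anyone.

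**Working it through.** **The plan's own figure.** Inputs from Sample size calculation: difference 109 − 105 = 4 mm, SD 5 mm, and "The sample size was calculated to provide an 80% power (α = 0.05"). The two-sample normal formula gives 2 × (1.96 + 0.84)² × 5² / 4² ≈ 24.5, so 25 per group. The two-sample t test needs 26, and a paired t test with zero correlation between sides needs 27. The stated 30 is not reproduced, but it exceeds all of these. Power at 30 pairs is 0.85 by the paired t test at zero correlation. The point below does not depend on how 30 was reached.

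**Model.** Let D be the within-patient difference between the two sides for one distance, b its biological SD, and e the SD of one reading's random error. Errors are assumed independent across readings, visits and sides. With m readings averaged per occasion:

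- change from baseline (2 occasions × 2 sides): Var(D) = b² + 4e²/m
- 48 h values only (2 sides): Var(D) = b² + 2e²/m

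The equivalent number of pairs with two readings instead of one is 30 × Var(D; m = 1) / Var(D; m = 2).

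**Assumed values.** The article gives neither b nor e. Assumed ranges: b = 3 to 5 mm, e = 1 to 2 mm.

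**Change contrast.**

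- Middle case, b = 4, e = 1.5: variance 16 + 9 = 25 with one reading, 16 + 4.5 = 20.5 with two. SD falls from 5.00 to 4.53 mm. The 95% half-width, 2.045 × SD / √30, falls from 1.87 to 1.69 mm. Equivalent pairs: 30 × 25 / 20.5 = 36.6.
- Smallest gain, b = 5, e = 1: 30 × 29 / 27 = 32.2.
- Largest gain, b = 3, e = 2: 30 × 25 / 17 = 44.1.

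**48 h values only.**

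- b = 5, e = 1: 30 × 27 / 26 = 31.2.
- b = 3, e = 2: 30 × 17 / 13 = 39.2.

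**Three distances averaged first, then a change contrast.** Independent error SD falls by √3, so e = 1 to 1.5 mm becomes about 0.6 to 0.9 mm.

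- b = 5, averaged error 0.6: 30 × 26.44 / 25.72 = 30.8.
- b = 3, averaged error 0.9: 30 × 12.24 / 10.62 = 34.6.
- Carrying e = 2 mm through (averaged variance 4/3) with b = 3: 30 × 14.33 / 11.67 = 36.9.

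**Effect on power.** Take the SD of change per side as 5 mm including single-reading error, 30 pairs, a 4 mm difference and a paired t test:

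| Correlation between sides | e (mm) | One reading | Two readings |
|---|---|---|---|
| 0 | 1 | 0.850 | 0.863 |
| 0 | 2 | 0.850 | 0.904 |
| 0.5 | 1 | 0.988 | 0.993 |
| 0.5 | 2 | 0.988 | 0.999 |

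**The case against.** The strongest reply is that nothing here is wrong. Replicate readings are often left to a measurement manual, the edema method comes from a cited source that is not at hand, and examiners are trained and checked for agreement. This stands in part: no contradiction or false figure is shown. But the article does fix a count for its primary outcome, and that count equals the number of distances. Training and an agreement check on outside volunteers help to control and describe reliability, but they do not average out the random error left in the trial readings.

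A second reply is that the trial is not short of precision. This stands. The planning SD of 5 mm is an observed SD and would normally already contain reading error, so a reader who infers that single readings erode the planned power goes beyond the documents.

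Three other stronger readings are tempting and should be resisted:

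- That the error enters the contrast four times. This holds only for a change-from-baseline comparison, which the article does not specify; the sample size rests on 48 h values, where the error enters twice.
- That the full single-reading error reaches the primary result. If the three distances are averaged, independent error variance is already cut to a third.
- That mouth opening is read once per visit. That would be an inference from silence, since no number of readings is given.

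Finally, repeat readings by one examiner leave untouched any systematic difference between the pre-operative and post-operative examiners, and any landmark error that both readings share. This also stands.

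**Conclusion.** The point holds as an optional, cheap improvement to the edema measurement. On the plain reading of Study outcomes each distance is read once, and averaging two independent readings halves the random-error part of the variance whichever contrast is used.

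The total gain runs from small to moderate: about 32 to 44 equivalent pairs for a change contrast, 31 to 39 for a 48 h contrast, and about 31 to 35 if the distances are averaged first with averaged error SD 0.6 to 0.9 mm. All of these rest on assumed reading error and biological SD and on independent errors. If the true reading error is well below 1 mm, the benefit is negligible.

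**What to change.** In Study outcomes (Edema), state that at each visit the blinded examiner for that visit reads each of the three facial distances twice, removing and replacing the tape between readings, and that the mean of the two enters the analysis. Covering the first value before the second reading helps keep the two independent. The paired readings also give the reading error in mm within the trial: the SD of the differences divided by √2.

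No rule for a third reading is needed. A trigger such as a 2 mm discrepancy has no basis in the article, and with e = 1.5 mm it would fire for about 35% of pairs of readings (2 / (1.5 × √2) = 0.94 SD).

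For mouth opening, state the number of readings; duplicates there are optional.

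Cost: 3 distances × 3 visits × 2 surgeries = 18 extra tape readings per patient, space for them on the case report form, and a little more time and handling of a sore face at day 2. No extra visit, device or staff is needed.
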